## Methods: participants, interventions, and outcomes

### Study setting {9}

This study is recruiting patients admitted to the Department of Neurosurgery of the University Hospitals Leuven (UZ Leuven), AZ Sint-Jan Brugge, and UZ Gent for endoscopic endonasal transsphenoidal procedures.

### Eligibility criteria {10}

Before initiation of any study procedures, participants (or their legal representative) must provide written informed consent (Additional file 2). Inclusion criteria are patients with lesions in the sellar or parasellar region with a minimum age of 18 years (Table 1). As this study includes a strict follow-up scheme with an additional visit, patients can only enroll if they agree to adhere to the follow-up schedule.

**Table 1 Tab1:** Eligibility criteria

Inclusion criteria	Exclusion criteria
Age ˃18 years	Age ˂18 years
Lesions of the sellar/parasellar region	Any underlying rhinological condition which may interfere with the obtained results
Informed consent signed	Participation to other clinical studies with drugs or medical devices
Willingness to adhere to visit schedule	

Patients with any underlying rhinological condition that may interfere with the obtained results, for example, nasal polyps, cannot be included. Participation to other clinical trials with study drugs or devices is another exclusion criterion.

### Who will take informed consent? {26a}

The neurosurgeon will inform the patients about the study at the time of planning the elective surgery. The study coordinator sends the information brochure beforehand. Trained study staff obtains the informed consent before the surgery, i.e., at the day of hospital admission which is usually 1 day before the surgery. Specialized consent forms are available for interpreters and — in case the patient is not capable to give consent — for legally authorized representatives. In such cases, it is the physician who determines the individual’s capacity to give consent.

### Additional consent provisions for collection and use of participant data and biological specimens {26b}

There are no plans for additional studies using the data collected in this trial. No biological specimens are collected.

## Interventions

### Explanation for the choice of comparators {6b}

At present, commercially available fibrin sealants are considered the gold standard for dural closure reinforcement after EETA. Tisseel® (Baxter, Deerfield, IL, USA) and TachoSil® (Corza, Düsseldorf, Germany) are used as standard of care in endoscopic transsphenoidal skull base reconstruction at UZ Leuven, UZ Gent, and AZ Sint-Jan Brugge. TachoSil® is approved by the European Medicines Agency (EMA) and Food and Drug Administration (FDA) for this indication.

### Intervention description {11a}

A team of neurosurgeons and otorhinolaryngologists perform the surgery according to local standards. If a patient is assigned to be treated with L-PRF, the use of commercially available fibrin sealants for sellar closure is not allowed. However, if deemed necessary by the surgeon, additional autologous (pericranium, muscle, fat grafts…) or allogenic (fascia lata) and hemostatic materials (cellulose sponges such as Spongostan® (Ethicon Biosurgery, Johnson and Johnson, New Brunswick, NJ, USA), Floseal® (Baxter, Deerfield, IL, USA), or Surgicel® (Ethicon Biosurgery, Johnson and Johnson, New Brunswick, NJ, USA)), can be used in both groups.

The L-PRF membranes are prepared during surgery. In order to ensure protocol adherence, the L-PRF preparation is performed by the study coordinator for study subjects assigned to treatment with L-PRF. In order to guarantee an optimal membrane formation, timing is of particular importance in this procedure. Therefore, the arterial line is flushed and immediately 20 mL of arterial blood is collected in a sterile syringe, transferred to two sterile 10-mL glass tubes (A-PRF®, Process for PRF, Nice, France), and instantaneously put in a centrifuge at 2700 rpm (400 g) (IntraSpin®, Intra-Lock, Boca Raton, FL, USA). During the transfer to the glass tubes and the start of the centrifugation, a second batch of 20 mL arterial blood is collected in a sterile syringe. This batch is transferred to 10-mL glass tubes as well, while the first centrifugation process is interrupted, and for ensuring a precise timing, the tubes are added into the centrifuge when decelerated. Then the centrifuge is instantly restarted at 2700 rpm for 12 min. If deemed necessary, an additional 20-mL syringe can be collected to fill two more 10-mL glass tubes and to be added to the centrifuge in a similar way.

After the centrifugation process, the presence of a dense clot right above the red blood cell layer in the tubes is verified. If these are not present, the tubes are put aside for 10 min and inspected again. The tubes are opened and presented to the scrub nurse for removing the clot with sterile forceps. The clot is placed in an Xpression Box® (Intra-Lock, Boca Raton, FL, USA) and gently compressed by placing the compression plate and the lid on top. After 5 min, the membranes are ready for surgical application by placing them on the dural defect. If necessary, the membranes can remain in the Xpression box® for up to 3 h until application. An instruction video of the L-PRF preparation process is available at http://doi.org/10.5281/ZENODO.8095217 [13].

### Criteria for discontinuing or modifying interventions {11b}

After allocation to the experimental or control arm, several circumstances—specified as perioperative exclusion criteria- can still lead to excluding the patient from the study. A patient allocated to the control arm may be excluded in case of a clear indication for a hypersensitivity reaction to commercially available fibrin sealants. Patients allocated to L-PRF treatment may be excluded if the L-PRF preparation process fails or if the product is considered of insufficient quality. In case the surgeon identifies other intraoperative findings that may constrain the conduct of the study procedure the subject can be excluded as well, to ensure optimal patient care in that situation. For example, when the damage to the dura is exceptional, the surgeon may opt for a multilayer reconstruction using multiple grafts, commercially available sealants, and autologous materials. Furthermore, study participants can withdraw from the study at any moment, implying that all subsequent study procedures and data collection are discontinued.

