## Background and rationale {6a}

The endoscopic endonasal transsphenoidal approach (EETA) to the skull base is a minimally invasive surgical technique that is used to treat a wide range of conditions affecting the skull base, such as pituitary tumors, suprasellar tumors and other diseases of the skull base. EETA is performed through the nasal cavity, without the need for an open craniotomy or facial incision, which leads to a faster recovery, reduced postoperative pain, and a lower risk of complications. However, the nasal cavity is a delicate and complex area that requires precise surgical techniques and can be susceptible to bleeding and inflammation. Additionally, recent advancements in endoscopic endonasal approaches (EEA) for skull base lesions have resulted in a significant increase in the extent and complexity of skull base defects, demanding more elaborate and novel reconstruction techniques to improve healing and prevent reconstruction failure. One major complication of EETA is postoperative cerebrospinal fluid (CSF) leakage. Our recently published systematic review, summarizing data from 113 studies, showed an average postoperative CSF leakage rate of 4.1% in endoscopic transsphenoidal surgeries [2]. A well-known risk factor for postoperative CSF leak is the presence of intraoperative leakage, in case of malignancy or, in cases where a thinned arachnoid herniates into the sella. As the pituitary is located in the diaphragma sellae, a double fold of the dura, large tumors may extend through the central opening of the diaphragm, resulting in a typical dumbbell shape, with an increased risk of CSF leak.

Postoperative leaks may require revision surgeries and/or external CSF drainage. Adequate dural closure is necessary to prevent CSF leak-related complications such as infections and intracranial hypotension. Currently, commercially available fibrin sealants, including Tisseel® and Tachosil®, are considered the gold standard for reinforcement of dural closure, due to their hemostatic, adhesive, and sealant properties [3]. However, problems regarding efficacy, cost, and safety have been reported [4, 5]. As such, commercially available fibrin sealants are expensive and may risk inducing hypersensitivity reactions.

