### Sample size {14}

Sample size calculation was performed according to the primary outcome, using an online power calculator for binary outcome non-inferiority trials (Sealed Envelope Ltd. Available from: https://www.sealedenvelope.com). This is a non-inferiority trial with a binary outcome using a one-sided alpha 0.05 and 80% power. The assumed success rate is 94.3% in the control arm, based on center-specific experience as well as the literature [14]. Data on the use of L-PRF for this indication is limited, but we assume a 95% success rate based on prior feasibility studies [8–10].

The statistical hypothesis for testing the treatment difference is presented as follows; H_0_: Δ ≤  − 0.07 tested against the alternative hypothesis H_A_: Δ >  − 0.07, where Δ is the difference between the success rates of experimental and control condition and − 0.07 is the non-inferiority difference. The non-inferiority limit was set at 0.07 considering (a) reported CSF leakage rates without commercially available fibrin sealant averaging 17.2% [15] and (b) important additional benefits of L-PRF compared to commercially available fibrin sealants including the completely autologous nature (eliminating immune reactions), presence of immunologic cells and reduced costs.

Based on this power calculation, 212 patients need to be included, 106 in each group. In order to account for potential missing follow-up information, failure of L-PRF preparation, or non-adherence to the allocation (expected drop-out rate less than 2%), 220 subjects will be enrolled, 110 in each group.

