### Adverse events reporting and harms {22}

Harms and adverse events that may be expected in the study population include diabetes insipidus, anterior pituitary insufficiency, and nasal septum perforation. During hospitalization, harms will be systematically collected from documentation of clinical and radiological examinations, and daily nursing reports in the electronical patient files. At the outpatient follow-up visits (FU1-4), harms will be collected based on anamnesis and clinical examination. Additionally, three open-ended questions will be presented to the subjects:Did you suffer from any complaints?Have you been ill?Have you taken any medication?

During the study, all adverse events are recorded and notified to the sponsor in an annual progress report. In agreement with the local law, serious adverse events are reported immediately, after first knowledge, to the sponsor and ethical committee, accompanied by detailed written reports. A serious adverse event is defined as any untoward medical occurrence or effect that results in death, is life-threatening, requires hospitalization or prolongation of existing hospitalization, results in persistent or significant disability or incapacity, or is a congenital anomaly or birth defect. Such serious adverse events will be reported in the final manuscript of the study. The sponsor shall keep detailed reports of all adverse events which are reported. For reported death of a subject, the investigator shall supply the institutional Ethical Committee with any additional information requested.

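### Control patients may be excluded after allocation for hypersensitivity to the sealant, which conflicts with the all-randomised ITT set and may leave the safety comparison incomplete

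*Protocol article*

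**What the plan says.** All references are to the protocol article.

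- **Criteria for discontinuing or modifying interventions {11b}.** Circumstances that arise once the arm is assigned "can still lead to excluding the patient from the study". For the control arm: "A patient allocated to the control arm may be excluded in case of a clear indication for a hypersensitivity reaction" to the sealant. The other arm has a different trigger: "Patients allocated to L-PRF treatment may be excluded if the L-PRF preparation process fails" or the product is judged inadequate. A third route, other intraoperative findings, is open to the surgeon in either arm. The section says that data collection ends for participants who withdraw. It does not say what happens to the follow-up of those who are excluded.
- **Who will be blinded? {17a}.** Surgical staff cannot be blinded and learn the arm after incision.
- **Handling of non-adherence and missing data {20c}.** The ITT set holds every randomised patient whether or not the protocol was followed. Per-protocol and as-treated sets are also planned. The primary endpoint is expected to be complete.
- **Sample size {14}.** "The non-inferiority limit was set at 0.07 considering" two grounds: (a) "reported CSF leakage rates without commercially available fibrin sealant averaging 17.2" per cent, and (b) further benefits of L-PRF. The benefits listed are "the completely autologous nature (eliminating immune reactions"), the presence of immunologic cells, and lower cost.
- **Background and rationale {6a}.** One motive for the trial is that "commercially available fibrin sealants are expensive and may risk inducing hypersensitivity reactions".
- **Adverse events reporting and harms {22}.** The section opens with examples of what is foreseen: "Harms and adverse events that may be expected in the study population include diabetes insipidus, anterior pituitary insufficiency, and nasal septum perforation". All adverse events are recorded; serious ones are promised for the final manuscript. Table 2 schedules adverse event assessment from the surgery visit onward.

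**The concern.** A rule that removes patients after randomisation, in one arm, for a reason tied to that arm's product gives up the comparability that randomisation provides. The ITT analysis in {20c} can be carried out as defined only if these patients are still followed for the 3-month leak outcome, and {11b} speaks of exclusion from the study, not from treatment.

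The trigger is also the event class that the trial holds against the comparator. Avoiding immune reactions is one reason given for tolerating up to 7 points of lost success, and safety against the sealants is a stated aim. If control patients who react can leave the study, the safety comparison may understate reactions in the control arm, and their later course may go unobserved. That error would run against L-PRF. For the leak endpoint the direction of any bias is unknown.

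**Working it through.** **1. The plan's own figure.** Inputs from {14}: control success 0.943, L-PRF success 0.95, margin 0.07, one-sided alpha 0.05, power 80%.

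n per arm = (1.645 + 0.842)² × (0.943 × 0.057 + 0.95 × 0.05) / (0.07 + 0.007)² = 6.183 × 0.10125 / 0.005929 = 105.6, rounded up to 106. The total is 212, as stated. Power is 80.1% at 106 per arm and 81.4% at the 110 per arm to be enrolled.

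**2. How many controls could be affected.** The documents give no reaction rate, so the rates below are assumptions. Expected cases = 110 × rate. The chance of at least one is 1 − (1 − rate)^110.

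| Assumed rate | Expected cases in 110 controls | Chance of at least one |
|---|---|---|
| 0.5% | 0.55 | 42% |
| 1% | 1.1 | 67% |
| 2% | 2.2 | 89% |
| 5% | 5.5 | 99.6% |

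At the lower rates, one or two exclusions could be every such event in the trial.

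**3. Effect on power.** Power = Φ(0.077 / SE − 1.645), with SE² = 0.943 × 0.057 / n_control + 0.95 × 0.05 / 110. One control lost: 81.3%. Five lost: SE = 0.0307 and power is 80.6%. Power is not the issue.

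**4. Effect on the leak comparison.** At the assumed 5.7% control failure rate, two or three controls carry 0.11 to 0.17 expected leaks (2 × 0.057 and 3 × 0.057). As bounds for five exclusions with 94.3% success in the remaining 105: control success among all 110 would be 0.943 × 105 / 110 = 90.0% if all five leaked, and (0.943 × 105 + 5) / 110 = 94.6% if none did. Exclusion could therefore flatter the control arm by up to 4.3 points or penalise it by about 0.3. The first extreme is implausible, since hypersensitivity is not part of the leak endpoint, but without follow-up neither can be ruled out.

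**5. Worst case for safety.** Suppose 5 of 110 controls react (4.5%) and all five are dropped from the safety table as well. The table would show 0 of 105, with a one-sided 95% upper bound of 1 − 0.05^(1/105) = 2.8%, below the rate that occurred. This needs every case to be excluded and none tabulated, which the text permits but does not require.

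**6. The two meanings of the trigger.**
- *Known or anticipated hypersensitivity.* By randomisation, about as many such patients fall in each arm. They stay if allocated to L-PRF and may leave if allocated to control. Table 1 does not list the condition, although medical history is taken at screening. No reaction is hidden, but the exclusion depends on the arm.
- *A reaction in theatre.* It is an adverse event of the comparator, and exclusion puts the patient's later follow-up at risk.

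Both meanings conflict with {20c}.

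**7. Is removal meant literally?** Section {14} counts failed L-PRF preparation, one of the {11b} triggers, under drop-out when raising 212 to 220. At least one {11b} exclusion is thus budgeted as a lost patient. Hypersensitivity is not named there, though the item on non-adherence to allocation might cover it.

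**The case against.** A reader might infer that the trial deletes this harm by design and that nothing in it captures hypersensitivity. The documents do not support that. Exclusion is permissive; adverse events are assessed from the surgery visit; all are to be recorded; and excluding a patient does not erase an event already entered. The list of expected harms is introduced as examples, so the absence of hypersensitivity from it does not mean that it goes unrecorded. This objection stands. What remains is that only serious events have a stated commitment to publication, and no text says that excluded patients stay in the safety comparison.

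A reader might also infer that the margin loses its basis. Immune reactions are one item within ground (b), beside ground (a), the immunologic cells and cost. A margin is set from prior knowledge and need not be proved by the trial's own data, and 110 controls could not estimate a rare reaction precisely. This also stands.

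It can be said that {11b} merely feeds the per-protocol set, so that ITT is intact. That is a possible reading, but {11b} says that patients leave the study, and {14} treats one of its triggers as drop-out. The two sections need reconciling.

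Finally, screening out known cases would reduce the reactions seen in the control arm, and the other two routes in {11b} may bear more on the primary result. Both remarks are fair. Screening would, however, act on both arms alike, and the other routes do not make this one harmless.

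**Conclusion.** The point holds in limited form. {11b} allows a control-only exclusion from the study after allocation, by staff who know the arm. This conflicts with the ITT set and the complete primary endpoint expected in {20c}. It may hide or leave incompletely followed an event class that is one of several grounds for the 0.07 margin.

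The number affected is unknown: 0.55 to 5.5 of 110 controls under assumed rates of 0.5% to 5%. The loss of power is negligible, 0.8 points at most for up to five controls. The direction of any bias in the leak comparison cannot be determined. The documents do not show that reactions will be missing from the safety data, only that nothing prevents it. This is worth correcting before analysis; it does not by itself undermine the trial.

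**What to change.** 1. Reconcile {11b} with {20c}. State that a patient who meets the hypersensitivity criterion after randomisation stays in the study, is followed to 3 months and through the 1-year visit, is analysed in the allocated arm in the ITT analysis and the safety comparison, and is removed only from the per-protocol set. Which product is then used remains the surgeon's decision and is outside this point.
2. Report hypersensitivity reactions, serious or not, by allocated arm, recorded in the same way in both arms.
3. State what the trigger means. If it is a hypersensitivity known beforehand, assess it before randomisation in the same way for everyone, so that it cannot act on one arm only.
4. For patients already excluded under this clause, report their number by arm and recover the 3-month outcome and adverse events where consent allows.

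The cost is amendment wording, one screening question and one adverse event code. No change to the sample size is needed.

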**Methods/design:**

This multicenter, prospective randomized controlled trial aims to demonstrate non-inferiority of L-PRF membranes compared to commercially available fibrin sealants in EETA cases (1) without intra-operative CSF-leak as dural or sellar floor closure reinforcement and (2) in EETA cases with intra-operative CSF-leak (or very large defects) in which a classic multilayer reconstruction has been made, as an additional sealing. The trial includes patients undergoing EETA in three different centers in Belgium. Patients are randomized in a 1:1 fashion comparing L-PRF with commercially available fibrin sealants. The primary endpoint is postoperative CSF leakage. Secondary endpoints are identification of risk factors for reconstruction failure, assessment of rhinological symptoms, and interference with postoperative imaging. Additionally, a cost-effectiveness analysis is performed.

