## Assessment of interventions: blinding

### Who will be blinded? {17a}

The randomization is single-blinded, i.e., enrolled patients do not know which group they are allocated to. Blinding of surgical staff is not possible as L-PRF is clearly different from fibrin sealants. Bias of surgeons is reduced as much as possible by announcing the treatment arm only after surgical incision. Reporting bias during hospital follow-up is reduced as the paramedics at the neurosurgery hospitalization department do not have access to the randomization code. The ENT specialist performing postoperative endoscopic examinations and applying the crusting score is blinded. Researcher’s bias during follow-up visits is reduced by reblinding subject allocation after surgery. For analysis, group allocation will only be released after the statistical analysis has been performed.

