### Methods in analysis to handle protocol non-adherence and any statistical methods to handle missing data {20c}

The results will be analyzed according to the following principles: the “intention-to-treat” (all randomized participants, irrespective of protocol adherence), the “per protocol” (only participants that were treated according to the protocol), and the “as treated” (all participants according to the treatment they received) principles. These three analyses will be compared to show how a lack of data possibly impacts the results. For the primary endpoint, no missing data are expected. For secondary endpoints (cost-effectiveness evaluation), the predictive mean of the other values within the arm will be used.

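### Exclusion from the study after allocation, partly for arm-specific reasons, conflicts with the all-randomised intention-to-treat set and leaves the comparison open to selection bias

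*Protocol article*

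**What the plan says.** Section {11b} (criteria for discontinuing or modifying interventions) lists perioperative criteria that can remove a patient from the study once the arm has been allocated. There are three routes:

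- Control arm only: a clear indication of hypersensitivity to the commercial sealant.
- L-PRF arm only: "Patients allocated to L-PRF treatment may be excluded if the L-PRF preparation process fails or if the product is considered of insufficient quality".
- Either arm: intraoperative findings that, in the surgeon's view, constrain the study procedure, with exceptional dural damage as the example.

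The arm is telephoned to theatre during surgery (Implementation {16c}). Section {17a} says surgical staff cannot be blinded and relies on "announcing the treatment arm only after surgical incision" to limit bias.

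The sample-size section {14} adds patients as follows: "In order to account for potential missing follow-up information, failure of L-PRF preparation, or non-adherence to the allocation". The expected rate is below 2%, and 212 becomes 220.

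Section {20c} defines the ITT set as "all randomized participants, irrespective of protocol adherence", adds per-protocol and as-treated analyses, and expects no missing data for the primary endpoint.

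**The concern.** An ITT analysis of all randomised patients needs a leak outcome for each of them. Section {11b} speaks of exclusion from the study, not only from the allocated sealant. Section {14} points the same way: preparation failure and non-adherence are not losses under ITT, yet extra patients are enrolled to make up for them. Read together, {11b} and {14} treat as lost the patients whom {20c} promises to keep.

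The reasons are also unequal. Product failure can arise only in the L-PRF arm, because {11a} has L-PRF prepared only for patients assigned to it, so that exclusion always follows a known allocation. The discretionary route can also be used with the arm known. Announcing the arm after incision does not protect here, because these exclusions come after the announcement.

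At stake is whether the trial compares the two strategies as allocated, or only the patients in whom each allocation worked out. With few expected events, the difference could reach the non-inferiority conclusion.

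**Working it through.** **1. The plan's own sample size.** Inputs, all from section {14}: "non-inferiority trial with a binary outcome using a one-sided alpha 0.05 and 80% power"; "The assumed success rate is 94.3% in the control arm"; for L-PRF, "we assume a 95% success rate based on prior feasibility studies"; margin 0.07.

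n per arm = (1.645 + 0.842)² × (0.943 × 0.057 + 0.95 × 0.05) / (0.07 + 0.007)² = 105.6, rounded up to 106, or 212 in total. This matches the plan. A 2% loss gives 212 / 0.98 = 216.3, so 217; the 220 enrolled covers losses up to 1 − 212/220 = 3.6%. The sample size is not in dispute.

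**2. Events.** Expected failures with 110 per arm: control 110 × 0.057 = 6.3; L-PRF 110 × 0.05 = 5.5. One leak moves an arm's rate by 1/110 = 0.91 points, which is 13% of the 7-point margin.

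**3. How few leaks separate success from failure.** Miettinen-Nurminen score test against −0.07, 110 per arm, 6 control leaks:

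| L-PRF leaks | One-sided p | Non-inferior at 5%? |
|---|---|---|
| 5 | 0.010 | yes |
| 6 | 0.021 | yes |
| 7 | 0.040 | yes |
| 8 | 0.071 | no |

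If one of the 8 L-PRF patients who leak is excluded (7 of 109), p = 0.042 and non-inferiority is met. A Wald test changes sides at the same place (0.028 at 7, 0.058 at 8).

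**4. Type I error.** Put true L-PRF success at the boundary, 0.943 − 0.07 = 0.873, so 110 × 0.127 = 13.97 failures are expected. Remove k L-PRF patients with failure risk q. The documents give neither k nor q, so both are assumptions; 17.2% is borrowed from the plan's quoted leak rate without commercial sealant.

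- Remaining failure rate r = (13.97 − kq) / (110 − k)
- Apparent difference d = (1 − r) − 0.943
- SE = √[0.943 × 0.057/110 + r(1 − r)/(110 − k)]
- Type I error = Φ[(0.07 + d)/SE − 1.645]

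Example, k = 2 and q = 50%: r = 12.97/108 = 0.1201; d = −0.0631; SE = 0.0383; Φ(0.180 − 1.645) = 7.15%.

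| Excluded, all from L-PRF | q = 17.2% | q = 50% |
|---|---|---|
| 0 | 5.0% | 5.0% |
| 2 | 5.2% | 7.15% |
| 5 | 5.6% | 12.0% |

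The direction depends on q. With k = 2 and q = 5.7% (the control rate), r = 13.856/108 = 0.1283, d = −0.0713, SE = 0.0390, and the error falls to 4.7%. In this model exclusions favour L-PRF only if those removed have a higher leak risk than the arm's average.

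**5. Power.** At the design rates, power is 81.4% with 110 per arm and 80.8% after losing 4 L-PRF patients. The issue is bias, not precision.

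**The case against.** A reader might infer that the ITT analysis cannot be run and that the comparison is biased towards L-PRF. The documents do not support that.

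- **Follow-up.** Section {11b} ends data collection explicitly only for participants who withdraw. It is silent on perioperative exclusions, and the as-treated analysis in {20c} presupposes that some patients who did not receive their allocated product are kept. This stands: the text is in conflict, but it does not prove that outcomes are lost.
- **Direction.** Preparation failure is tied to product quality, not to leak risk, and the article does not say what such a patient then receives. If it were commercial sealant, their leak risk might be near the control rate, and keeping them in the L-PRF arm could pull the arms together. Hypersensitivity removes control patients, and the discretionary clause covers both arms. This stands too.
- **Size.** The one-leak reversal is a borderline case. About 5.5 L-PRF leaks are expected, and from 5 or 6 leaks it would take two or three further leaks, not one, to lose non-inferiority. Drop-out is expected below 2% for all causes together. That is an expectation and not a cap, but the article gives no basis for assuming many exclusions.
- **Population.** The abstract includes cases "in EETA cases with intra-operative CSF-leak (or very large defects) in which a classic multilayer reconstruction has been made", which could be read as the very cases {11b} lets surgeons exclude. But {11a} allows extra grafts in both arms, so multilayer repair alone is no ground for exclusion. The example in {11b} is exceptional damage where commercial sealants may be added, and {11a} bars those for sellar closure in the L-PRF arm. What remains is an undefined boundary between very large and exceptional defects.

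None of this removes the conflict between {11b} and {14} on one side and {20c} on the other. A statistical analysis plan can define the sets, but it cannot supply outcomes that were never collected.

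**Conclusion.** The point holds as a conflict within the protocol article that leaves the primary comparison open to selection bias. Sections {11b} and {14} treat certain randomised patients as lost, {20c} counts them, and nothing says they are followed for CSF leak. If they are not, the ITT analysis is incomplete.

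At the exclusion numbers the plan itself anticipates, the effect is small to moderate: two exclusions, all from L-PRF, put the type I error between 5.2% and about 7% under the assumed leak risks. It grows if exclusions are more numerous or more selective. The number excluded and their leak risk are not in the documents, so neither the direction nor the size of any bias can be stated as fact. It is still worth correcting before analysis, because the safeguard is cheap and uncollected outcomes may not be recoverable.

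**What to change.** - In {11b}, state that these events end the allocated study intervention but not study participation.
- Follow every randomised patient who has not withdrawn consent for CSF leak to 3 months, and count each in the allocated arm in the ITT primary analysis.
- Apply the perioperative exclusions to the per-protocol set only, and report their number and reasons by arm.
- In {14}, stop treating preparation failure or non-adherence as a loss from the ITT analysis. The step from 212 to 220 then covers missing leak status only, and the sample size need not change.
- Reconcile the abstract, {11a} and {11b} on very large and exceptional defects. How such cases are managed clinically is for the investigators and is not questioned here.

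The cost is a change of wording and follow-up of what should be a handful of extra patients. The ITT result may come out slightly less favourable to L-PRF.
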